#### *Health economic analysis*

Service use is to be measured with the Client Service Receipt Inventory. Costs will be calculated by combining service use data with available unit cost information. The following comparisons between the groups at 12- and 18-weeks will be assessed: (i) proportion of patients using each service included in the Client Service Receipt Inventory; (ii) mean number of contacts with each service for those with at least one contact; (iii) mean cost of each service (including those with no contacts); (iv) mean total cost.

The first three comparisons will be descriptive with no tests of significance. The main focus will be on the comparison of total costs and for this we will use a regression model with total cost as the dependent variable, the group identifier variable as an independent variable, and baseline costs as an additional independent variable. We will visually check the distribution of the regression residuals; if these do not approximate a normal distribution, we will use bootstrapping methods with 1,000 repetitions to generate 95% confidence intervals.

A cost-consequences analysis will be conducted by viewing costs alongside efficacy measures. Cost effectiveness will be assessed by combining costs with the primary outcome of activity levels, using cost effectiveness planes, which will indicate the probability that the intervention is (i) cost saving with better outcomes, (ii) cost saving with worse outcomes, (iii) cost increasing with worse outcomes or (iv) cost increasing with better outcomes. These will be constructed by saving the 1,000 bootstrapped regression coefficients representing cost differences described previously and 1,000 bootstrapped regression coefficients representing outcome differences (change in activity levels) and plotting these against each other as a scatterplot.

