#### *Randomization*

Following informed consent and completion of baseline assessments, individuals will be randomized to one of the treatment arms by the study coordinator. This will be conducted independently of the trial team by the King’s Clinical Trials Unit, using an online randomization system. Randomization will be carried out at a 50:50 ratio and will be at the level of the individual and stratified by main problem focus (anxiety; depression), using random permuted blocks (varying in size from three to six).

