### Analysis

#### *Statistical analysis*

The outcomes of most interest are successful recruitment, randomization, quality and fidelity of the delivery of treatment and participant’s compliance with the protocol, including both treatment adherence and completion of research assessments. Descriptive statistics will be used to summarize these feasibility aspects and confidence intervals will be constructed for respective performance indices.

However, we will also carry out some efficacy comparisons of CBT + TAU versus TAU. These analyses will adhere to the intention-to-treat principle, with data from all participants entered into the analysis, including from all those who drop out of therapy (that is, those who do not attend at all or who cease therapy) or who miss some therapy sessions. Every effort will be made to follow up all participants in both arms for research assessments, and the analysis will use, where appropriate, statistical techniques for handling missing data. Linear mixed modelling will be used to compare mean outcomes between the treatment arms at each of the two post-treatment time points. More specifically, the outcome measured at the post-treatment time points will feature as the dependent variable and stratifier (main problem focus), pre-randomization outcome measure score, time, treatment arm and time × arm interaction term as explanatory variables. Correlation between the two repeated measures per person will be taken into account by including a subject varying random intercept. Therapist effects will be modelled by a further random intercept term that varies at the level of the therapist. A detailed statistical analysis plan has been written by the trial statistician.

If noncompliance with the active treatment (GOALS) is high, a complier average causal effect analysis will be considered, to estimate efficacy [30]. This might be warranted, since an intention-to-treat analysis estimates the effect of randomization group; that is, the treatment’s effectiveness only equals the treatment’s efficacy if every participant also receives the treatment that is allocated to them. Conventional per-protocol or as-treated analyses have long tried to address this but are subject to selection bias.

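### The regressions behind the cost-effectiveness plane are not aligned with the efficacy model: the cost model omits the stratifier, and the effect axis is worded as change with no stated link to the baseline-adjusted analysis

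*Protocol article*

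**What the plan says.** The Health economic analysis section of the protocol article makes total cost the main comparison: "we will use a regression model with total cost as the dependent variable". The independent variables are "the group identifier variable as an independent variable, and baseline costs as an additional independent variable", and no others are named.

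For the cost-effectiveness plane, those bootstrapped cost coefficients are plotted against "1,000 bootstrapped regression coefficients representing outcome differences (change in activity levels". No covariates are listed for this second regression, and none are excluded.

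The Statistical analysis section treats the same primary outcome differently. There, "the outcome measured at the post-treatment time points will feature as the dependent variable", and the explanatory variables are "stratifier (main problem focus), pre-randomization outcome measure score, time, treatment arm and time" by arm, with random intercepts for subject and therapist. The Randomization section confirms that allocation is "stratified by main problem focus (anxiety; depression" being the two strata.

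**The concern.** Activity level is both the primary efficacy outcome and the effect axis of the plane. One section models the post-treatment score adjusted for baseline and stratifier. The next speaks of change, and neither refers to the other nor explains the difference.

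The plane's output is a set of four quadrant probabilities, which depend directly on the centre and spread of the bootstrap cloud. If the effect axis came from a change score with no baseline term, the cloud would be wider than it need be. Its centre could also sit away from the activity effect in the efficacy table, and readers would see two estimates of one effect with no pre-stated reason.

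Separately, the cost model as written leaves out the factor on which randomization was stratified, although the trial's own efficacy model includes it.

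**Working it through.** **1. The three models side by side**

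| | Efficacy model | Cost regression | Outcome regression for the plane |
|---|---|---|---|
| Dependent variable | Post-treatment score | Total cost | Change in activity |
| Own baseline as covariate | Yes | Yes | Not stated |
| Main problem focus | Yes | Not listed | Not stated |

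Two things are documented: the stratifier is not listed for cost, and the dependent variable for activity differs. Whether the change regression includes baseline activity is left open.

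**2. Inputs, and the plan's own figure**

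The Sample size section gives Time Budget means of 52.3 and 61.8, SD 11.2, 28 per group and two-sided alpha 0.1. The difference is 61.8 − 52.3 = 9.5, and 9.5/11.2 = 0.848, which the article gives as 0.8. With d = 0.8 and 28 per group, power is 90.5% by the t test (91.1% by the normal approximation). Allowing for 15% loss, 56/0.85 = 65.9, hence 66. The stated figures reproduce, so SD 11.2 and 28 per arm are used below, with the SD taken as equal at baseline and follow-up. The correlation r between baseline and follow-up is not given. It is assumed to lie between 0.3 and 0.9.

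**3. Precision if baseline activity is not a covariate**

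- SE of the change-score difference = 11.2 × √(2(1 − r)) × √(2/28)
- SE of the baseline-adjusted difference = 11.2 × √(1 − r²) × √(2/28)
- Variance ratio = 2(1 − r)/(1 − r²) = 2/(1 + r)

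| r (assumed) | SE, change score | SE, baseline-adjusted | Variance ratio |
|---|---|---|---|
| 0.3 | 3.54 | 2.86 | 1.54 |
| 0.5 | 2.99 | 2.59 | 1.33 |
| 0.7 | 2.32 | 2.14 | 1.18 |
| 0.9 | 1.34 | 1.31 | 1.05 |

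**4. Precision if baseline activity is a covariate**

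Regressing change on arm and baseline gives the same arm coefficient as regressing the post-treatment score on arm and baseline. Subtracting baseline from the dependent variable alters only the baseline coefficient. In simulation the two arm coefficients agreed to rounding error (largest difference about 5 × 10⁻¹⁵). On this reading the table in step 3 does not apply.

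**5. How far the two estimates can differ in one trial**

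Without a baseline term, the change-score and baseline-adjusted estimates differ by about (1 − r) times the chance baseline difference between arms. That difference has SD 11.2 × √(2/28) = 2.99 points. At r = 0.5, an imbalance of one SD separates the estimates by 0.5 × 2.99 ≈ 1.5 points, or 1.5/9.5 ≈ 16% of the planned effect. A simulation with 28 per arm and 3,000 runs per scenario gave SDs of the gap of about 0.19, 0.14 and 0.09 outcome SDs at r = 0.3, 0.5 and 0.7. Both estimates were centred on the same true effect.

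**6. The stratifier**

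In the same simulation, arms were balanced within strata and the stratum shifted the post-treatment score by 0 to 0.5 SD. Omitting the stratifier left the empirical SE essentially unchanged. For example, at r = 0.5 with a 0.5 SD shift, it was 0.2388 without the stratifier and 0.2384 with it. This was done on the activity scale; the article gives no cost data to repeat it for costs.

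**The case against.** The strongest objection is that the article never says the change score is unadjusted. A reader might infer this, because a baseline term is named for costs while for activity baseline appears only through the word change. The documents do not support stating it as fact. No covariate list is given for the outcome regression, and the cost regression beside it does adjust for its own baseline, which could equally suggest the same for activity. The phrase may also be loose shorthand for improvement. This objection stands, so the variance ratios are conditional on a reading that the text allows but does not state.

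A reader might also infer bias. That does not follow: under randomization both estimators target the same mean difference.

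Three further points have weight. The article condenses a fuller plan and mentions a separate statistical analysis plan, so the absence of a covariate list is not itself a fault. Omitting the stratifier costs almost no precision in the check above, and nothing in the article shows that main problem focus predicts cost. The plane is also descriptive, and it belongs to a pilot whose main objective is feasibility.

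What remains rests on what the article does fix: a cost model with two named covariates and no stratifier, and an effect axis worded differently from the efficacy model for the same outcome.

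**Conclusion.** The point holds in a limited form and is minor. The cost regression as written omits the randomization stratifier that the efficacy model includes, and the effect axis is not tied to the baseline- and stratifier-adjusted analysis.

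If baseline activity is left out of the outcome regression, the effect estimate has 5% to 54% more variance than the adjusted one for r from 0.9 to 0.3, an SE about 3% to 24% larger. It may also depart from the efficacy estimate through chance imbalance. If baseline activity is included, that loss is zero. The sizes rest on an assumed r, equal SDs of 11.2 and 28 evaluable patients per arm. The article's remark that the measure has high test-retest reliability would favour the upper part of the range for r, but it gives no correlation over the trial's interval.

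The consequence is inefficiency and inconsistency, not a biased comparison. The stratifier part rests on consistency with the trial's own model rather than on any material gain in precision.

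**What to change.** In each bootstrap resample, fit:

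- total cost on arm, baseline cost and main problem focus;
- Time Budget score at the time point used for the plane on arm, baseline Time Budget score and main problem focus.

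In the Health economic analysis section, replace the reference to change in activity with the baseline-adjusted difference in activity.

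The covariates are already collected and the change is one of wording. Small differences from the efficacy estimate may remain, because that model uses both post-treatment time points and has subject and therapist random intercepts. One sentence saying so would prevent the two figures from being read as contradictory.

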#### *Qualitative analysis*

All interviews will be audiotaped, transcribed and analyzed qualitatively using thematic analysis [31], and indexed using NVivo software. Interviews conducted by study assistant psychologists and service user consultants will be analyzed separately, but outcomes will be compared. Thematic analysis has a number of key steps, including generating initial data-driven codes, searching and refining key themes, and defining and naming these themes before summarizing and producing a final report. To check reliability, at least 15% of the transcriptions will be second-coded and checked for agreement, to ensure that the coding framework is deemed reliable (at least 80% agreement).

## Discussion

Anxiety and depression are commonly present in people with psychosis and lead to inactivity and difficulties in achieving personal goals. Cognitive behavioural therapy for psychosis, which can be effective for emotional problems in psychosis [5,6,32], is a formulation-based therapy, delivered by highly trained therapists over 16 to 20 sessions, and, although recommended by NICE, is not widely available [33]. There are, however, effective brief protocol-based interventions, graded exposure and behavioural activation, which use cognitive behavioural principles and methods, for these problems. We have adapted these to address the specific needs and problems of people with psychosis, while ensuring a focus on personal recovery goals, and achieved promising results in our pre-pilot study [15]. The advantages of the GOALS approach are that it is brief and that the frontline mental health workers who are in regular contact with people with psychosis in care settings can be readily trained in its delivery. There is therefore scope for developing an effective intervention, which can be made widely available at low cost, improving access to psychological therapies for this client group. This is the first trial of the GOALS intervention. The study also aims to finalise the training curriculum and the treatment manual, which we intend to publish and make available in electronic form in the future. The trial is funded until August 2015 and the results will be available in 2016. If this intervention proves clinically feasible and demonstrates preliminary evidence of efficacy, a large multi-site trial will be warranted.

## Trial status

Participants began to enter the trial in April 2013. Recruitment will continue until December 2014.

## Abbreviations

CBT: cognitive behaviour therapy; GOALS: ‘Getting On top of Anxiety and Low mood’; NHS: National Health Service; NICE: National Institute for Health and Care Excellence; SMART: specific, measurable attainable, relevant and time-bound; TAU: treatment as usual.
